### Monitoring and intervention adherence plan

The project is led by the core research team comprising the principal investigators, lead researchers, and a doctoral student. The project team is advised by a steering group comprising the core research team and stakeholders. The core research team holds regular meetings to monitor study progress. During intervention planning and development, two meetings with stakeholders, comprising a school PE teacher, a representative of the teacher union, the head of the in-service PE teacher training program, and the head of the city Education Department, will take place to maximize acceptability and adherence to the trial. In addition, the project team will hold regular meetings with stakeholders to discuss content and administration of the intervention. The PE teacher trainers who will deliver the autonomy support training for teachers in the intervention group will receive a familiarization session with the research team during which they will receive instruction on the intervention aims and training materials. They will also have the opportunity to discuss the rationale and expected outcomes of the program to maximize quality of delivery. To increase responsiveness and engagement of the PE teachers, we will use several motivational techniques such as facilitating their autonomous goals or outcomes and clarifying expectations. We aim to offer concrete, clear, and relevant feedback during the teacher training sessions. In terms of intervention fidelity [61, 62], the observation of PE teachers’ lessons during the course of the intervention will serve as a means to ensure fidelity of the intervention delivery to students during the implementation period. In cases where lower than expected compliance with the intervention is identified indicating problems with fidelity, we will create a dichotomous variable representing compliance with intervention and include it as a control variable in our path analyses to test whether fidelity had a significant effect on changes in out-of-school physical activity and other outcomes. Finally, we will content analyse the teachers self-evaluation forms completed after the teacher training period, and the infographic posters produced by each teacher during training that are designed to summarize their learning. These will serve as means to ensure fidelity of the intervention training delivery to participating PE teachers.

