#### Additional measures

##### Observation of teacher autonomy supportive behaviours

Teacher’s use of autonomy-supportive behaviours in their lessons will be assessed using the tool for observing autonomy-supportive behaviours in teachers (TOAST) developed specifically for this study. The tool is a modified and extended version of checklist [49] for rating teachers’ autonomy-supportive and controlling behaviours in classroom contexts. The tool was augmented to include additional content based on the list of autonomy supportive and controlling behaviours identified in previous research [18]. The checklist was also developed to closely correspond to the autonomy supportive behaviours and strategies targeted in the autonomy support training program. The tool comprises three main categories of teacher behaviour: providing instructions, praise and encouragement, and dealing with misbehaviour. Each category is coded as autonomy supportive or controlling. Two additional categories, links with out-of-school physical activity and provision of an explanation or rationale, are coded as autonomy supportive only. The tool requires observers to note the frequency of behaviours displayed by the observed teacher in each category. Overall autonomy supportive and controlling behaviours in the first three categories, and autonomy supportive behaviours in the final two categories, are calculated by summing the frequencies of the observed behaviours in each category over the observation period. The open-source BORIS software is used for coding observations [50]. Research assistants blind to the purpose of the study will be trained by project researchers to code of the audio recordings from the lessons of participating teachers’ at baseline and at the scheduled follow-up data collection occurrences.

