### Data analysis

Multilevel structural equation modelling using the Mplus, v. 8.0 software [59] will be used to test our hypotheses. All analyses will be performed using intention-to-treat analysis and supplemented by per-protocol analyses for all planned outcome variables [60]. Where data is missing for the psychological variables, we will impute missing values using linear interpolation if the data is confirmed missing completely at random. We expect to have data on our primary and secondary outcome measures, as well as mediating measures, at pre-trial and at the allotted follow-up occasions after the delivery of the intervention (post-trial, and at the one-, three-, and six-month follow up data collection occasions after the implementation period). We also expect to have self-report data on parenting from students and their parents or guardians at pre-trial. Student data will be nested within school and teacher/class, and therefore variance in outcome variables may be attributable to school-level and class-level variation as well as variation between students attributable to the intervention itself. Effects of the intervention on study outcomes can be interpreted at the student level after controlling for school- and class-level effects. Our longitudinal design enables also the examination of potential trajectories in the development of outcome variables. We will test the model at each of the follow-up time points with students’ out-of-school physical activity as the primary dependent variable, the intervention condition as a dummy-coded independent variable (1 = intervention group; 0 = control group), and the psychological variables (perceived autonomy support from teachers, autonomous motivation in PE and out-of-school physical activity, attitudes, subjective norms, perceived behavioural control, intentions), as simultaneous predictors. We will statistically control for each of model variables from the previous time point using the standardized residual scores.

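### Adding a compliance variable when fidelity is low changes what the condition coefficient estimates, and the article does not confine that model to a supplementary role

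*Protocol article*

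**What the plan says.** The rule is in Methods, Monitoring and intervention adherence plan. Its trigger is "In cases where lower than expected compliance with the intervention is identified indicating problems with fidelity". Its action is "we will create a dichotomous variable representing compliance with intervention and include it as a control variable in our path analyses". Its stated purpose is "to test whether fidelity had a significant effect on changes in out-of-school physical activity and other outcomes". The fidelity information comes from lesson observation, which "will serve as a means to ensure fidelity of the intervention delivery to students during the implementation period".

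Other sections set the context:

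- **Data analysis.** The path model at each follow-up regresses out-of-school physical activity on condition (1 for intervention, 0 for control) together with the trans-contextual model constructs. The section commits all analyses to intention-to-treat, with per-protocol analyses as a supplement.
- **Procedure and data collection methods; Wait-list control group.** Intervention teachers apply the techniques for one month. Control teachers receive an unrelated 4-hour training, and get the autonomy-support training straight after the three-month follow-up.
- **Observation of teacher autonomy supportive behaviours.** Recordings are coded "at baseline and at the scheduled follow-up data collection occurrences".

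The article does not say how control teachers are coded on the compliance variable, and it does not label the model containing it as supplementary.

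**The concern.** Whether a teacher complies is known only after randomisation, and autonomy-supportive teaching is the first step through which the intervention is meant to work. A covariate of this kind, entered beside condition, is not a neutral adjustment. It splits the randomised contrast into two pieces, neither of which compares the groups as randomised.

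At stake is the reading of the condition coefficient in the situation the rule is written for, namely imperfect delivery. If that coefficient were taken as the effect of the programme, part or all of the effect delivered through complying teachers would be missing from it. The coefficient for compliance would not fill the gap, because teachers who comply may differ from those who do not in ways that affect students' activity anyway. The rule also covers outcomes other than physical activity, so the paths from condition to the mediators could be altered in the same way.

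**Working it through.** The article attaches no figure to this rule, so there is none to reproduce. The check is algebra, followed by an illustration on the trial's own structure.

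**Step 1: what the coefficients mean.** Let μ0, μC and μN be the mean outcomes in control classes, complying intervention classes and non-complying intervention classes. Let p be the proportion of intervention classes that comply. Fit outcome = a + b × condition + c × compliance.

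- No compliance term: b = p·μC + (1 − p)·μN − μ0, which is the intention-to-treat contrast.
- Compliance added, controls coded 0: b = μN − μ0 and c = μC − μN.
- Compliance added, controls coded 1: b = μC − μ0 and c = μC − μN.

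Under either coding, b is no longer the contrast between the groups as randomised, unless μC = μN.

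**Step 2: illustration.** From the article: 29 teachers with one class each, and 502 students, so 502/29 ≈ 17 per class. Assumed, because the article gives no values: a 15 to 14 split of classes, intraclass correlation 0.05, an effect of 0.30 SD in complying classes, and compliance of 40%, 60% or 80%. Take μ0 = 0, controls coded 0.

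| Effect in non-complying classes | b without compliance (40 / 60 / 80%) | b with compliance |
|---|---|---|
| 0 | 0.12 / 0.18 / 0.24 | 0.00 |
| 0.10 SD | 0.18 / 0.22 / 0.26 | 0.10 |
| 0.30 SD | 0.30 / 0.30 / 0.30 | 0.30 |

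For example, at 60% with 0.10 SD in non-compliers: 0.6 × 0.30 + 0.4 × 0.10 = 0.22. With compliance in the model, b is the non-complier effect itself, 0.10. A simulation of class means (3,000 replicates per setting) agreed with every cell to within about 0.01. With controls coded 1 and no effect in non-compliers, b was 0.30 at all three compliance rates, which overstates the intention-to-treat values of 0.12 to 0.24.

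**Step 3: precision.** In the first row of the table, the simulated standard error of b is about 0.126 without the compliance term. With it, the values are 0.137, 0.157 and 0.206 at 40%, 60% and 80%. The reason is that b then rests on only 9, 6 or 3 non-complying classes. As a check at 80%, the variance of a class mean is 0.05 + 0.95/17 = 0.106, and √[0.106 × (1/3 + 1/14)] ≈ 0.207. These values carry no separate school-level variance.

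**Step 4: when fidelity is observed.** The adherence section relies on lessons observed during the intervention. The procedure section schedules recordings at pre-trial, at post-trial (after the implementation phase), and at three and six months, with none at one month. On the text shown, no recording falls inside the implementation month.

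**The case against.** The strongest reply is that the rule has a limited purpose. The sentence says the variable is there to test for a fidelity effect, so the coefficient of interest in that model is the one for compliance. The Data analysis section separately commits to intention-to-treat, and nothing in the adherence section withdraws it. This stands. A reader might infer that the plan abandons the intention-to-treat comparison, but the article does not say so, and a model without the compliance variable may well be reported. What remains is that the adjusted model is not set apart from the effectiveness analysis, and that its compliance coefficient is a non-randomised comparison.

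A reader might also infer that low fidelity will produce a null or reversed intervention effect. The documents do not support that as a prediction. A null requires non-complying teachers to achieve nothing. A reversal requires, in addition, some teacher characteristic that drives both compliance and outcome, for which the article gives no size. The figures above also describe a two-term regression, whereas the planned model already holds the mediators beside condition, so its condition coefficient is a direct effect before any compliance term is added.

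Three further points stand in part. Coding controls as 0 is not written: lessons are recorded in both arms, and the Discussion expects Finnish teachers to be fairly autonomy-supportive already, so a score based on observation could class some controls as compliant. The variable would still be post-randomisation and on the causal path. Next, controls are trained before the six-month occasion, so the structural tie between compliance and the intervention arm holds only through three months. Finally, the trigger is observed fidelity, not outcomes, and the coders are blind to allocation. The absence of a threshold is the kind of detail an article leaves to a fuller document.

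**Conclusion.** The point holds in a limited form. In any model containing the compliance variable, the condition coefficient is not the intention-to-treat effect, and the article does not restrict such a model to a supplementary role. With controls coded 0, the coefficient loses the part of the effect that depends on compliance: all of it if non-compliers produce no effect, some of it if they produce a smaller effect, and none if the two groups have equal outcomes. The change in meaning follows from the algebra and is certain. Its size rests on assumed effects, compliance rates and intraclass correlation, and on the coding of controls. The separate mismatch between observing lessons during the intervention and recording them afterwards is a matter of wording to reconcile, subject to the timeline figure and the additional file, which are not shown.

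**What to change.** - State that the compliance variable is left out of every model used to estimate the intervention effect, and that the intention-to-treat model without it is reported whatever fidelity is observed.
- Pre-specify fidelity as a supplementary analysis, and say how control teachers are coded. One option is a comparison within the intervention arm, labelled observational. The other is a complier-average causal effect with randomised school allocation as the instrument and clustering by school.
- If the second option is chosen, state its assumption that allocation has no effect through non-complying teachers. If that fails, the estimate is too large: a uniform effect of 0.20 SD with 50% compliance would give 0.20/0.5 = 0.40. State too that it will be imprecise with 11 schools.
- Restrict either analysis to occasions before controls are trained, that is, up to and including the three-month follow-up.
- Reconcile the adherence section with the recording schedule, so that it is clear which lessons the fidelity measure describes.

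The cost is a few sentences of analysis text. No new data are needed. The price of the supplementary analysis is either confounding by teacher differences or low precision, which is why it should not carry the main conclusion.

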### Data management

The University of Jyväskylä will own the research data. Consent forms and paper questionnaires will be stored in locked cabinets in the lead project researcher’s office. Digital data will be stored on password-protected centrally-managed cloud-based storage drives of the Information Management Center at the University of Jyväskylä. All datasets will be de-identified with participants allocated a unique code number. Data files will be managed by core research team members appointed to this task. The key used to identify participants’ data will be stored separately from data files and will only be accessible to designated members of the core research team members. Results will be reported in articles published in established international scientific journals and presentations in scientific and professional congresses. The researchers will target open access publishing and comply with the University of Jyväskylä recommendation of parallel publishing in the University open access digital repository. Results will also be communicated through traditional and social media for the public.

## Discussion

School PE is an existing network with considerable potential for the delivery of interventions to promote physical activity to a captive audience of young people. Such interventions are also consistent with PE curricula to promote lifelong physical activity and health. However, relatively few studies have examined the effectiveness of school-based PE interventions in promoting out-of-school physical activity. The goal of the proposed study outlined in this protocol is to address this gap in the literature by testing the effectiveness of a theory-based intervention delivered in PE to promote lower secondary school students’ physical activity outside of school. The intervention will capitalize on the trans-contextual model [6, 10], a motivation model which specifies the processes by which teachers’ support for students’ self-determined or *autonomous* motivation in school translates to their autonomous motivation, beliefs, and intention toward, and actual participation in, physical activity outside of school.

The intervention will make a unique contribution to knowledge in four areas: (i) it will test the effectiveness of a theory-based in-school intervention delivered by PE teachers in promoting lower secondary school students’ physical activity participation outside of school, which has seldom been demonstrated; (ii) it will evaluate how the intervention works in promoting students’ out-of-school physical activity participation through effects of intervention on key constructs from the trans-contextual model; (iii) it will outline the development and implementation of a cost-effective, replicable theory-based teacher training program to train teachers to use autonomy-support techniques in their PE lessons and promote out-of-school physical activity; and (iv) it will evaluate the long-term effectiveness of the intervention in promoting physical activity behaviour through one, three, and six-month post-intervention follow-up of behavioural and theory-based outcomes.

Although school PE has been identified as an important existing network in which messages and interventions promoting out-of-school physical activity participation could be promulgated, interventions to promote out-of-school physical activity through school PE are rare and these studies often only have limited follow-up periods of behavioural outcomes. For example, a previous study [63] demonstrated the effectiveness of a PE delivered intervention aimed at promoting physical activity participation in high school students. However, the study adopted a relatively brief intervention, relied exclusively on self-reported physical activity measures, and only adopted a relatively short term follow-up of students’ behaviour. Our proposed intervention will advance this research by developing a comprehensive autonomy support training program with an associated set of training materials, use accelerometry to verify self-report measures of physical activity, and conduct a longer-term follow up of intervention effects.

One of the key strengths of the current study is the theoretical basis and the provision to test the mechanisms of effectiveness of the intervention. The current intervention is based on the trans-contextual model [10], which provides a clear basis for the mechanisms of the proposed intervention effects. Specifically, we expect the autonomy-supportive intervention delivered by PE teachers to lead to changes in students’ autonomous motivation in school and outside of school, and their beliefs and intentions toward physical activity outside of school. We will test the effects of the proposed intervention on these theory-based constructs as secondary outcomes in the current intervention. Furthermore, because we plan to collect long-term follow up data we will be able to ascertain whether changes in the psychological constructs as a result of the intervention are maintained over time. The current study is the first to specifically design an intervention using this model and to test the theory-based mechanisms of intervention effects.

One of the potential challenges for the study, raised by external stakeholders, is that Finnish PE teachers are likely to be relatively autonomy-supportive at baseline. Autonomy-supportive teaching is currently emphasized both in the Finnish national PE curriculum and in the Finnish PE teacher training curriculum [7]. This raises the possibility that intervention effects will not be as strong as interventions in other contexts where autonomy support is not part of teacher training [24]. However, despite teachers’ previous exposure to instruction on how to support students’ autonomy, it is unclear to what extent teachers apply these techniques. For example, it is likely that teachers may use these techniques inconsistently, coupled with other, more controlling techniques. Research has demonstrated that even when teachers use autonomy support techniques, if they also use controlling techniques concurrently, it will undermine students motivation and lead to maladaptive outcomes [64]. The potential for previous exposure to autonomy support training notwithstanding, the current program focuses on training teachers’ to use these strategies with greater intensity, specificity, and consistency, so we expect to see changes in the relevant indicators of autonomy support in students post-intervention. Another potential challenge, raised by external stakeholders and teacher educators, is resistance by PE teachers towards supporting students’ autonomy in PE lessons. A key strategy to deal with this challenge is to convince PE teachers that supporting students’ autonomy should not be equated with independence, and autonomy support does not lead to lack of discipline or ‘chaos’ in the classroom [34].

One of the challenges facing interventionists is difficulty in replicating interventions. This is important given the well-publicized need for high-quality replications of interventions that have demonstrated effects to provide converging evidence for effectiveness across contexts and populations. This endeavor is hampered by poor reporting of intervention protocols and content [65]. A strength of the current study is the provision of complete and detailed intervention materials to maximize transparency and potentials for replication. We will provide open access to the materials for the autonomy support training program including the materials used to train teachers and an accompanying manual providing explicit step-by-step instructions for facilitators to run courses to train teachers in autonomy supportive techniques. In addition, study measures and instruments will also be made available. The materials will be made available on the project website: https://osf.io/s4b2g/.

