### Sample size

A statistical power analysis was conducted to estimate the required sample size for student data based on a path analysis according to published recommendations [56]. The analysis was based on a model in which the primary outcome variable of student’s participation at each post-intervention follow-up occasion was regressed on the intervention condition (dummy coded as 1 = received intervention, 0 = received control) and constructs from the trans-contextual model (perceived autonomy support, autonomous motivation in PE and out-of-school, attitudes, subjective norms, perceived behavioural control, and intentions) as simultaneous predictors. Statistical power (beta) was set at 0.90 and statistical significance level (alpha) was set at 0.05, and confidence intervals of 0.068 and 0.080 for the root mean square error of approximation fit index based on previous trans-contextual models [9]. The analysis indicated that a student sample size of 286 is required to detect the effect size based on model fit. Based on typical attrition rates of 40% reported in the literature in multiple follow-up studies of physical activity [57, 58] we aim to recruit 476 student participants at baseline (*n* = 238 participants per intervention group).

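### The protocol promises to show whether intervention effects are maintained, but its models, run per occasion and adjusted for the previous time point, do not estimate that and would shrink a maintained effect toward zero

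*Protocol article*

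**What the plan says.** In the Discussion, the paragraph on theory-based mechanisms states that with long-term follow-up data "we will be able to ascertain whether changes in the psychological constructs as a result of the intervention are maintained over time". Earlier in the Discussion, the fourth listed contribution is that "it will evaluate the long-term effectiveness of the intervention in promoting physical activity behaviour through one, three, and six-month post-intervention follow-up".

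The analysis that has to deliver this is under Methods, Data analysis. It uses multilevel structural equation modelling, and the authors write: "We will test the model at each of the follow-up time points". Out-of-school physical activity is the dependent variable, and intervention condition and the psychological variables are simultaneous predictors. The adjustment is then fixed: "We will statistically control for each of model variables from the previous time point using the standardized residual scores". One sentence looks across occasions: "Our longitudinal design enables also the examination of potential trajectories in the development of outcome variables". It names no model, no condition-by-occasion term and no contrast between arms.

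Under Procedure and data collection methods, the wait-list teachers receive the autonomy-support training immediately after the three-month occasion, so the six-month comparison has no untreated control.

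**The concern.** Whether an effect is maintained is a question about the later intervention effect relative to the post-trial one. A set of occasion-specific models gives neither that difference nor its standard error.

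The adjustment adds a second problem. At post-trial, the previous occasion is the pre-trial baseline, which randomization protects from any effect of training. At one month, the previous occasion is post-trial, which already contains the effect. The condition coefficient then describes further separation of the arms since post-trial. If the arms stay equally far apart, much of that gap is absorbed by the covariate. A later coefficient near zero is therefore compatible with complete maintenance, yet in a table of results by occasion it would look like decay.

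At stake is the statement on durability for the psychological constructs, and for physical activity wherever the same models are used to describe persistence.

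**Working it through.** **What the protocol supplies.** Sample size states: "Statistical power (beta) was set at 0.90 and statistical significance level (alpha) was set at 0.05". The effect-size input is "confidence intervals of 0.068 and 0.080 for the root mean square error of approximation fit index". So the 0.90 concerns model fit, not the intervention effect. The recruitment target reproduces: 286 / (1 − 0.40) = 476.7, against 476 stated. The 286 itself cannot be checked because the model degrees of freedom are not given. No power for the intervention effect and no between-occasion correlation appear, so both are assumed and varied below. Tests are taken as two-sided at 0.05; the protocol does not state sidedness.

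**Step 1: effect of adjusting for the previous occasion.** Assume unit variance, correlation ρ between occasions (compound symmetry) and a constant intervention effect d. The condition coefficient at the later occasion, given the earlier one, is d − ρd = d(1 − ρ). The residual standard deviation is √(1 − ρ²). The expected z therefore falls by the factor (1 − ρ)/√(1 − ρ²) = √[(1 − ρ)/(1 + ρ)].

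Take an effect that an unadjusted single-occasion test would detect with 80% power (expected z = 1.960 + 0.842 = 2.80) or 90% power (z = 1.960 + 1.282 = 3.24):

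| ρ | share of effect left, 1 − ρ | z factor | power left, from 80% | power left, from 90% |
|---|---|---|---|---|
| 0.3 | 0.7 | 0.734 | 54% | 66% |
| 0.5 | 0.5 | 0.577 | 37% | 47% |
| 0.7 | 0.3 | 0.420 | 22% | 28% |

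The effect is fully maintained in every row. Under this model the post-trial estimate and the adjusted later estimate are uncorrelated, since ρ − ρ = 0. The chance of a significant post-trial result followed by a non-significant one is then a product. Starting from 80% power it is 0.80 × (1 − 0.538) = 37% at ρ = 0.3 and 0.80 × (1 − 0.218) = 63% at ρ = 0.7.

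This leaves out the psychological variables entered as simultaneous predictors, clustering, and the baseline adjustment of the post-trial model. It shows the direction and rough size, not a forecast.

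**Step 2: if significance verdicts were compared without that adjustment.** With a constant effect and equal power p at two occasions, the chance that the verdicts conflict is 2 × [p − P(both significant)], from the bivariate normal distribution:

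| power | ρ = 0.2 | ρ = 0.5 | ρ = 0.6 | ρ = 0.8 |
|---|---|---|---|---|
| 50% | 44% | 33% | 30% | 21% |
| 80% | 29% | 23% | 20% | 14% |
| 90% | 17% | 13% | 12% | 9% |

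**Step 3: precision of the direct contrast.** At ρ = 0.6 the standard error of the difference between two occasion effects is √[2(1 − 0.6)] = 0.894 of a single-occasion standard error. If the effect halves from a post-trial z of 2.8, the contrast has expected z = 1.4/0.894 = 1.57, or 35% power. From z = 3.6 it is 1.8/0.894 = 2.01, or 52% power. The contrast addresses the right quantity but would often miss a real halving.

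**The case against.** The strongest reply has four parts.

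First, the protocol nowhere says that maintenance will be judged by comparing p-values. A reader might infer that this is the only route left, but the text does not support it: the authors mention trajectories, and a fuller analysis plan may specify a longitudinal model. This stands, and Step 2 is therefore conditional. It does not remove the point, because the article states both a promise and a specific analysis, and that analysis answers a different question. The trajectories sentence says what the design permits, not what will be fitted.

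Second, maintained could simply mean that a difference between arms is still present later, which needs no contrast between occasions. That is a fair reading, but a model adjusted for the previous occasion does not estimate the effect still present either.

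Third, a reader might infer that the fourth listed contribution also fails. It promises only long-term effectiveness, which a suitably adjusted estimate at a later occasion can address. The Discussion sentence about the psychological constructs is the one that asks for more.

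Fourth, a reader might take a single conflict rate as a property of this trial. No such figure follows from the protocol. The rate depends on assumed power and correlation, falls below 20% at 90% power, and describes unadjusted tests rather than the planned models.

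**Conclusion.** The point holds in limited form. The protocol promises to establish maintenance, and the analysis it fixes estimates neither the change in effect between occasions nor the effect still present at the later one. Under compound symmetry a fully maintained effect would appear at about (1 − ρ) of its size: 70% at ρ = 0.3, 30% at ρ = 0.7. The tendency is toward a false reading of decay.

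If separate, unadjusted verdicts were compared instead, conflict under a constant effect would arise in about 14–44% of trials (power 50–80%, ρ 0.2–0.8) and about 9–17% at 90% power. All of these figures rest on assumed power and correlation. This is a matter to correct before analysis; it does not invalidate the trial or its post-trial comparison.

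**What to change.** For physical activity and for each psychological construct, specify one repeated-measures multilevel model over post-trial, one month and three months, with condition, occasion and their interaction. Adjust for the baseline value in place of the previous occasion. Stop this comparison at three months, because controls are trained immediately afterwards. Describe six-month results separately, as no longer set against an untreated control.

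Report the intervention effect at each occasion and the condition-by-occasion contrast, three months minus post-trial, each with a confidence interval. State that a change in significance between occasions will not be read as loss or gain of effect, and that a non-significant contrast alone will not be read as maintenance.

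The cost is a few sentences and a little more analysis, with no new data. The drawback is imprecision: about 35–52% power to detect a halved effect if post-trial z is 2.8–3.6 and ρ is 0.6. The interval, not the test, should carry the conclusion.
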